## Abstract

**Background:**

The majority of patients with head and neck squamous cell carcinoma (HNSCC) receive bilateral elective nodal irradiation (ENI), in order to reduce the risk of regional failure. Bilateral ENI, as compared to unilateral ENI, is associated with higher incidence of acute and late radiation-induced toxicity with subsequent deterioration of quality of life. Increasing evidence that the incidence of contralateral regional failure (cRF) in lateralized HNSCC is very low (< 10%) suggests that it can be justified to treat selected patients unilaterally. This trial aims to minimize the proportion of patients that undergo bilateral ENI, by using lymph drainage mapping by SPECT/CT to select patients with a minimal risk of contralateral nodal failure for unilateral elective nodal irradiation.

**Methods:**

In this one-armed, single-center prospective trial, patients with primary T1-4 N0-2b HNSCC of the oral cavity, oropharynx, larynx (except T1 glottic) or hypopharynx, not extending beyond the midline and planned for primary (chemo) radiotherapy, are eligible. After ^99m^Tc-nanocolloid tracer injection in and around the tumor, lymphatic drainage is visualized using SPECT/CT. In case of contralateral lymph drainage, a contralateral sentinel node procedure is performed on the same day. Patients without contralateral lymph drainage, and patients with contralateral drainage but without pathologic involvement of any removed contralateral sentinel nodes, receive unilateral ENI. Only when tumor cells are found in a contralateral sentinel node the patient will be treated with bilateral ENI. The primary endpoint is cumulative incidence of cRF at 1 and 2 years after treatment. Secondary endpoints are radiation-related toxicity and quality of life. The removed lymph nodes will be studied to determine the prevalence of occult metastatic disease in contralateral sentinel nodes.

**Discussion:**

This single-center prospective trial aims to reduce the incidence and duration of radiation-related toxicities and improve quality of life of HNSCC patients, by using lymph drainage mapping by SPECT/CT to select patients with a minimal risk of contralateral nodal failure for unilateral elective nodal irradiation.

**Trial registration:**

ClinicalTrials.gov Identifier: NCT03968679, date of registration: May 30, 2019.

## Background

The great majority of patients with head and neck squamous cell carcinoma (HNSCC) receive elective nodal irradiation (ENI) to both sides of the neck in order to reduce the risk of contralateral regional failure (cRF). However, there is increasing evidence that the incidence of cRF in lateralized HNSCC is very low (< 10%) [1–5]. Bilateral ENI, as compared to unilateral ENI, is associated with higher incidence of acute and late radiation-induced toxicity with subsequent deterioration of quality-of-life (QoL) [6–11]. One way to reduce the incidence and severity of these toxicities is by implementation of unilateral ENI, in patients where this can be justified.

The first SUSPECT study (ClinicalTrials.gov Identifier NCT02572661) investigated whether lymph drainage mapping (LDM) using Single Photon Emission Computed Tomography/Computed Tomography (SPECT/CT) was a safe and feasible method to exclude the contralateral neck from the elective irradiation fields, or, in case of contralateral lymph drainage, to tailor the contralateral ENI field only to the level containing the tracer accumulation [12, 13]. Large dose reductions to most organs at risk were realized (Fig. 1). Moreover, we found significant reductions of both short term (mucositis, dysphagia) and long term (xerostomia, dysphagia) toxicities (manuscript in preparation).

**Fig. 1 Fig1:**
[figure not shown]
Dose reduction to organs at risk. Boxplot of planned mean irradiation doses to organs at risk. For every patient treated within the SUSPECT-1 study, two plans were made: a unilateral plan based on the results of the SPECT/CT, that was used to treat the patient, and (for comparison purposes) a regular bilateral plan they would have been treated with outside the framework of the study. The mean doses to all these organs at risk were significantly lower in the unilateral plan, compared to the regular bilateral plan. Abbreviation: Gy: gray

Since around 20% of patients treated within the first SUSPECT study had contralateral tracer accumulation (usually in one neck level), a substantial proportion of patients still received an elective irradiation dose to one contralateral neck level. In studies investigating sentinel node procedures (SNP) for oropharynx and oral cavity carcinoma, contralateral sentinel nodes (SNs) were found in 8–40% of patients. However, the overall prevalence of tumor-positive contralateral SNs was only 0–2.5% [2, 4, 14, 15]. Some studies suggest the overall prevalence might be higher (around 10%) in larynx and hypopharynx carcinoma [5, 16]. Even so, elective irradiation to all contralateral draining sentinel nodes might still be overtreatment.

The aim of the current manuscript is to introduce the sequel to this study, the SUSPECT-2 study (ClinicalTrials.gov Identifier NCT03968679). Like the first SUSPECT study, the SUSPECT-2 study selects patients for unilateral treatment if they have no contralateral lymphatic drainage from the tumor site, but it modifies the original concept by performing a contralateral SNP in case of contralateral lymph drainage. Patients without pathologic involvement of those contralateral SNs are also treated unilaterally. Only when tumor cells are found in a contralateral SN the patient will be treated with standard bilateral ENI. Furthermore, the SUSPECT-2 study has expanded the inclusion criteria to include all patients with HNSCC without evident extension beyond the midline, regardless of the T-classification. It thus strives to further reduce the proportion of patients that undergo bilateral ENI.

### Study objectives and endpoints

#### Objectives

To investigate the contralateral regional failure rate after radiotherapy (with or without cisplatin-based chemotherapy, cetuximab or immunotherapy) for patients with HNSCC nor crossing the midline, treated with SPECT/CT-guided unilateral ENI.To investigate the toxicity of this treatment strategy, and the impact on patients’ quality of life.To investigate the prevalence of tumorpositive contralateral sentinel nodes in patients with HNSCC not crossing the midline.

#### Primary endpoint

Cumulative incidence of contralateral regional metastasis at 1 and 2 years after treatment.

#### Secondary endpoint

b.Early and late radiation-related toxicityc.Quality of life after treatment

#### Exploratory endpoint

d.Prevalence of (micro/macro) metastasis in contralateral sentinel nodes

## Methods

### Study design

This study has a one-arm, single-center prospective trial design. Patients eligible for this study will undergo SPECT/CT-guided LDM, and based on its findings either unilateral or bilateral ENI will be performed.

### In- and exclusion criteria

#### Inclusion criteria

Eligible for inclusion are patients who are planned for primary radiotherapy (with or without cisplatin-based chemotherapy, cetuximab or immunotherapy) for newly diagnosed primary HNSCC of the oral cavity, oropharynx, larynx (except T1 glottic) or hypopharynx. Eligible disease classification is T1-4 N1 for HPV-positive oropharyngeal cancer, and T1-4 N0-2b for all other tumors (American Joint Committee on Cancer Staging Manual, 8th edition). The tumor needs to be clinically lateralized (not crossing the midline) and histopathologically proven. Patients aged 18 years or older with a performance status of 0–1 (World Health Organization classification) can be included.

#### Exclusion criteria

The main exclusion criteria are clinically tumorpositive contralateral lymph nodes, distant metastatic spread, prior treatment for the current tumor, previous (chemo) radiotherapy or surgery in the head and neck area, and/or recurrent or second primary tumor.

### Pre-treatment evaluation

Standard pretreatment evaluation includes ultrasound of the neck and fine needle aspiration cytology (US-FNAC) performed by a dedicated head and neck radiologist, contrast-enhanced CT scan (and/or MRI), and FDG-PET (Table 1). During US, hypoechogenicity, round shape, border irregularity, a short axis greater than 5 mm, and loss of fatty hilus are considered signs of possible malignancy for which FNAC is performed to confirm or exclude lymph node metastasis. On MRI, a short axis > 10 mm, border irregularity with or without extension in adjacent structures and MRI signs of necrosis are considered signs of possible malignancy. On CT, a short axis > 10 mm, round shape, signs of necrosis, border irregularity with or without extension in adjacent structures are considered signs of possible malignancy. Only in case of a clinically negative neck on one side (N1-2b) or on both sides of the neck (N0), a patient is eligible for inclusion. After the initial work-up, a head and neck surgeon will assess the location and extent of the primary tumor during an investigation under general anesthesia, and will take a biopsy from the primary site.

**Table 1 Tab1:** Schedule of assessments

	Baseline	During RT	Follow-up					
			1st year^a^				2nd year^a^	3rd-5th year^a^
			12w^a^	6 m^a^	9 m^a^	12 m^a^	every 4 m	every 6 m
Standard of care:								
Physical examination	x	x	x	x	x	x	x	x
Flexible endoscopy	x		x	x	x	x	x	x
Toxicity	x	x	x	x	x	x	x	x
QoL-questionnaire	x		x	x	x	x	until 18th month^a^	
US-FNAC	x		x	x	x	x	when indicated	
CT or MRI^b^	x		x	when indicated				
FDG-PET	x		when indicated					
Investigation under anesthesia	x		when indicated					
RT planning CT	x							
Extra in SUSPECT-2:								
Signed informed consent	x							
Tracer injection and SPECT/CT	x							
Contralateral SNP	only when contralateral drainage is visualized on SPECT/CT							

^a^After end of radiotherapy

^b^According to our institutional guidelines, patients with oral cavity or oropharyngeal tumor are staged by MRI, while laryngeal and hypopharyngeal tumors are staged by CT

Abbreviations: *w* weeks, *m* months, *RT* radiotherapy, *US-FNAC* ultrasound-fine needle aspiration cytology, *SNP* sentinel node procedure

### Interventions

A flowchart of the study set-up is shown in Fig. 2. On the day of the endoscopy under general anesthesia, the patient will undergo the following procedures:
*Injection of radioactive tracer around primary tumor*. Either in the outpatient clinic using flexible endoscopy, or during the endoscopy under general anesthesia, the head and neck surgeon will perform biopsy from the primary tumor site, and will inject a hybrid tracer of indocyanine green (ICG) with (99 m)Tc-nanocolloid in a dose of 80 MBq in a volume of 0.4 cc with 0.05 mg nanocolloid (Nanocoll, Dutch GE Healthcare radiopharmacy, Leiderdorp, The Netherlands). The tracer will be divided in 5 depots, 4 in the mucosa around the primary tumor at 3 mm from macroscopic tumor edges, and one in the tumor itself, according to standard protocol used for surgical procedures of sentinel node biopsy in our institution.*Planar lymphoscintigraphy and SPECT/CT*. After the injection, radioactive tracer migration will be verified using static planar lymphoscintigraphic images followed by SPECT and low-dose CT (SPECT/CT) (40 mAs, 130 Kv) performed at the department of nuclear medicine in radiation treatment position using a personalized radiotherapy mask. Images will be acquired using a dual-head SPECT/CT gamma camera (Symbia T, Siemens, Erlangen, Germany), at 3 ± 1 h after administration, to allow for adequate tracer distribution with maximum sensitivity for contralateral drainage. Planar images are acquired from anterior, left anterior oblique with the head turned to the right, and right anterior oblique with the head turned to the left. SPECT acquisition parameters are 256 × 256 matrix, zoom of 1.0, 2 heads, 180° rotation with 20 views per head (30 s per view). Low-dose CT images are acquired for anatomical correlation with SPECT, and for attenuation correction and scatter correction of SPECT images. For image reading SPECT, CT and fused SPECT/CT are displayed using orthogonal multiplanar reconstruction, maximum intensity projection, and volume rendering. Both a radiation oncologist and nuclear medicine specialist will judge the planar and SPECT/CT images for detection of all sentinel lymph nodes considering their activity and anatomical localization. An example of SPECT/CT images combined with planar lymphoscintigraphy images is shown in Fig. 3. The location of any contralateral draining sentinel nodes is marked on the skin with a marker using a portable gamma camera (Sentinella; Oncovision, Valencia, Spain).

**Fig. 2 Fig2:**
[figure not shown]
Study flowchart. Flowchart of the SUSPECT-2 study design. Abbreviation: ^99m^Tc: Technetium-99 m

### Pathology examination of removed contralateral SNs

The SNs are fixed in 10% neutral-buffered formalin and three serial sections are cut every 150 μm through the block. At all levels a section is stained with haematoxylin and eosin (H&E) and anti-pan cytokeratin antibody AE1/3. If a metastasis is diagnosed, the size of the metastasis is classified as isolated tumor cells (size ≤0.2 mm), micrometastasis (size > 0.2 mm and ≤ 2 mm), or macrometastasis (size > 2 mm).

### Treatment: radiotherapy regimens

Patients participating in the study will follow the standard preparation procedures for radiotherapy planning, according to institutional guidelines. To the gross tumor volume, a 6 mm isotropic margin will be added to generate the Clinical Target Volume (CTV) of the primary tumor. Elective ipsilateral neck levels will include level I-V in case of node-positive disease and level II-IV in node-negative disease. According to international guidelines, the following tumor site-based exceptions are included [17]:
In patients with node-negative oral cavity cancer only level I-III will be electively irradiated.In patients with node-negative laryngeal and hypopharyngeal cancer, level IV will also be treated electively in case of subglottic extension > 1 cm, transglottic extension and extension into the apex of the piriform sinus.In patients with node-negative disease from all sites, the retropharyngeal space will be treated in tumors extending to the posterior wall of the pharynx/larynx and in tumor originating in or extending to the post-cricoid space.In patients with node-positive disease, the elective ipsilateral neck levels will also include the adjacent neck level, e.g. in patients with a positive node at the cranial part of level II, the pre-styloid space will also be treated electively.

The inclusion of a contralateral nodal irradiation field will be based on the findings of the LDM using SPECT-CT, and the pathologic examination in case a SNP was performed:
In case no contralateral drainage was seen on SPECT/CT and no contralateral SNP was performed, no neck levels are irradiated in the contralateral neck.In case a contralateral SNP was performed, and pathologic examination found no evidence of metastatic disease, no neck levels are irradiated in the contralateral neck.In case a contralateral SNP was performed and pathologic examination revealed macrometastases or micrometastases, contralateral levels II–IV are irradiated according to internationally accepted guidelines [17].In case a contralateral SNP was performed but the SN was not identified/detected, the elective irradiation will include the ipsilateral neck plus the contralateral neck level containing the tracer accumulation.

Subsequently, a 3 mm isotropic margin is added to the CTVs to generate the Planning Target Volume (PTV-ENI).

The organs at risk will be delineated according to the internationally accepted guidelines [18] and include the spinal cord, brainstem, cochlea, parotid glands, submandibular glands, thyroid gland, swallowing muscles, oral cavity, supraglottic region, and the larynx.
PTVprimary tumor = 70 Gy in 35 fractions of 2.0 GyPTVelective nodal irradiation = 54.25 Gy in 35 fractions of 1.55 Gy

Planning will be performed with a Simultaneous Integrated Boost technique using volumetric arc modulated radiotherapy. An accelerated fractionation schedule (6 fractions per week) will be used if radiotherapy is given alone. The 6th fraction shall be given as a second fraction on one of the weekdays with an interval of at least 6 h. When radiotherapy is combined with systemic therapy, conventional fractionation schedule will be applied (5 times per week). All patients receive daily online cone beam CT for positioning imaging.

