### Sample size estimation

The probability of cRF in carefully selected patients with lateralized HNSCC was estimated to be 2% at 2-years [19–21]. The preliminary results of the proof-of-concept study, the SUSPECT 1, showed that after a median follow-up of 30 months only one patient (2%) developed cRF when treated to one side of the neck. With the inclusion criteria expanded to allow for lateralized T4 tumors, we estimated the rate of cRF to be around 5% or lower. The study was designed to demonstrate a cRF rate ≤ 15%. The limit of 15% is motivated by the fact that an elective irradiation of the neck in case of HNSCC is indicated only when the chance of occult metastasis in the neck exceeds 15% [22–24]. Approximately 90 evaluable patients are required (exact test for a binomial proportion with H0: *p* = 0.15, HA: *p* = 0.05, power = 0.80, α = 0.05, two-sided). Evaluable patients mean those who are treated unilaterally. Patients who are treated bilaterally (patients with contralateral micro−/macrometastases or those with a failed SPECT/CT) will be regarded as not evaluable for the primary and secondary end points and will be replaced by including new evaluable patients. The accrual period of the study is estimated to be 48 months, based on an inclusion rate of at least 2 patients per month.

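### After a tumour-positive contralateral sentinel node the field is fixed at levels II–IV, so a positive node from level I or V leaves its own level unirradiated

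*Protocol article*

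**What the plan says.** The contralateral field is set by a short list in the protocol article, section Treatment: radiotherapy regimens. Two entries matter here.

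- Sentinel node removed and metastatic: if pathology "revealed macrometastases or micrometastases, contralateral levels II–IV are irradiated according to internationally accepted guidelines". No condition on tumour site or on the node's level is written.
- Sentinel node procedure done but node not found: "the elective irradiation will include the ipsilateral neck plus the contralateral neck level containing the tracer accumulation". This field follows the tracer, whichever level that is.

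The same section sets the ipsilateral volumes first: "Elective ipsilateral neck levels will include level I-V in case of node-positive disease and level II-IV in node-negative disease". A site exception follows: "In patients with node-negative oral cavity cancer only level I-III will be electively irradiated". For node-positive disease, "the elective ipsilateral neck levels will also include the adjacent neck level".

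The Background describes the positive branch without listing levels: "Only when tumor cells are found in a contralateral SN the patient will be treated with standard bilateral ENI". Oral cavity tumours are eligible (Inclusion criteria). Under Sample size estimation, patients treated bilaterally because of contralateral metastases "will be regarded as not evaluable for the primary and secondary end points and will be replaced by including new evaluable patients".

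**The concern.** In the positive branch the protocol irradiates the contralateral neck although the involved node has already been taken out. It therefore treats the remaining risk on that side as worth a course of elective irradiation. If the node came from level I or V, however, the one level where spread has been shown is left out, and no reason is given. The neighbouring rule, for a node that was not found, would cover that level.

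What is at stake is the treatment of individual patients: a clinician who follows the named levels exactly would leave a level with proven spread without elective dose. The trial's inference is not at stake.

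**Working it through.** The plan gives no figure on this point to reproduce. The check compares the two rules and then estimates how many patients could be affected.

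**Comparison of the two rules, by level of the contralateral sentinel node**

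| Level of the node | Node removed, metastatic: is that level in the field? | Node not found: is that level in the field? |
|---|---|---|
| I | No (field is II–IV) | Yes (tracer level) |
| II, III or IV | Yes | Yes |
| V | No (field is II–IV) | Yes (tracer level) |

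For a node within II–IV the positive branch is at least as generous, with three levels against one. The anomaly is confined to nodes outside II–IV. There, the level in question gets less cover when metastasis is proven than when the node was missed.

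**Number of patients**

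Inputs:
- Evaluable patients needed: 90 (Sample size estimation).
- Prevalence p of a positive contralateral sentinel node: for oropharynx and oral cavity, "the overall prevalence of tumor-positive contralateral SNs was only 0–2.5" per cent; for larynx and hypopharynx, possibly around 10% (both from the Background).
- Share q of those patients whose positive node lies outside II–IV: not given in the article. Every value of q below is an assumption.

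Formulas: patients treated to reach 90 evaluable, N = 90/(1 − p); sentinel-node-positive patients = N × p; affected patients = N × p × q; chance of at least one = 1 − (1 − p × q)^N. N leaves out patients replaced for other reasons, such as a failed SPECT/CT, who would raise it slightly.

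| p | N | Positive patients | q (assumed) | Affected, expected | Chance of at least one |
|---|---|---|---|---|---|
| 0% | 90 | 0 | any | 0 | 0% |
| 1% | 90.9 | 0.91 | 5% | 0.05 | 4% |
| 1% | 90.9 | 0.91 | 10% | 0.09 | 9% |
| 1% | 90.9 | 0.91 | 30% | 0.27 | 24% |
| 2.5% | 92.3 | 2.31 | 5% | 0.12 | 11% |
| 2.5% | 92.3 | 2.31 | 10% | 0.23 | 21% |
| 2.5% | 92.3 | 2.31 | 30% | 0.69 | 50% |
| 2.5% | 92.3 | 2.31 | 100% (ceiling) | 2.31 | 90% |
| 10% (whole cohort larynx/hypopharynx) | 100 | 10 | 5% | 0.5 | 39% |

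Example, fifth row: 90/0.975 = 92.3; 92.3 × 0.025 = 2.31; 2.31 × 0.05 = 0.12; 1 − (1 − 0.00125)^92.3 = 0.11.

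**Effect on the analysis**

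Patients in the positive branch are replaced and do not enter the primary or secondary analyses. Neither the count of contralateral failures nor its denominator changes with this rule.

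**The case against.** The strongest defence is that a different contralateral volume is a choice and not a contradiction. Three readings that a reader might infer go too far, and the defence is right about each.

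- *That II–IV conflicts with the protocol's own volumes.* Levels I–V and the adjacent-level rule are written for the ipsilateral neck, and the oral cavity volume of I–III for node-negative disease. A contralateral neck with a proven metastasis is neither. These volumes serve only as comparators. Carrying the oral cavity exception across literally would even remove level IV from a neck with proven spread.
- *That II–IV breaks the Background's promise of standard bilateral treatment.* The Background lists no levels, so a mismatch is an inference.
- *That II–IV departs from the cited guideline.* The guideline is not shown, and the reference to it may have been meant to bring in site-specific levels.

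Two further objections touch the point itself. First, the two branches differ: a missed node is still in the neck, while a positive one has been removed. That is true, and it means residual disease in the level is a risk and not proven. It does not explain the omission, because the protocol irradiates II–IV after the same excision. Second, a condensed article may leave target-volume detail to the full protocol or institutional guideline. This would answer a rule that said nothing about levels. This rule names them, and what it names leaves out the level of the positive node whenever that level is I or V.

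**Conclusion.** The point holds as a minor patient-safety correction. The stated rule can leave the level of a proven contralateral metastasis outside the field, while the adjacent rule would cover that level had the node been missed. This conclusion rests only on those two rules.

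Probably 0–1 patients are concerned. That figure depends on q, which the documents do not give, and on the article's prevalence range; even the ceiling for oral cavity and oropharynx is about 2.3 patients. The primary test, sample size and evaluable population are unaffected. The article does not show whether II–IV was a deliberate choice or a gap in wording.

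**What to change.** Amend the rule for a metastatic sentinel node to: *contralateral levels II–IV, plus the level from which the positive sentinel node was removed if outside II–IV*.

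This clause does not settle the case of an oral cavity tumour whose positive node lies within II–IV. The radiation oncologists should confirm whether level I is to be included there as well, without dropping level IV, and the answer should go into the same sentence. If II–IV alone is intended even for a positive node in level I or V, a short reason should be given.

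The cost is one clause and, in probably 0–1 patients, a slightly larger contralateral target volume with more dose to nearby organs at risk. No extra procedure, patient or analysis is needed.
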